## Abstract

**Background:**

Active aging has been established as a policy goal for aging societies. We define active aging at the individual level as striving for elements of well-being through activities in relation to a person’s goals, functional capacities and opportunities. Increasing evidence suggests that any meaningful activity is beneficial for different aspects of well-being in older people. The aim of the present randomized controlled trial is to test the feasibility and effectiveness of a one-year community-based intervention on active aging. The AGNES intervention aims at increasing older peoples’ participation in self-selected valued activities.

**Methods:**

The proposed study is a two-arm single-blinded randomized controlled trial. The intervention group receives individually tailored counselling for an active life (one face-to-face session, four phone calls and supportive written material) and the control group written general health information only. Two hundred older adults aged 75- and 80- year old, with intermediate mobility function and without cognitive impairment, living independently in the municipality of Jyväskylä, Finland, are recruited and randomized with a 1:1 allocation to the intervention and control group. Randomization is computer-generated stratified by sex and age. The primary outcome is active aging and secondary outcomes are well-being, depressive symptoms, quality of life, personal goals, mobility and physical activity. Measures are administered at pre-trial, mid-trial (at 6 months) and post-trial (12 months after baseline).

**Discussion:**

The AGNES intervention study will provide new knowledge on the effects of individualized counselling on active aging and the potential of older people to promote their own well-being.

**Trial registration:**

The trial is registered at ISRCTN - ISRCTN16172390: Promoting well-being through active aging.

## Background

Active aging is a widely accepted policy goal in Europe and other countries experiencing population aging. The European Union ranks countries according to the Active Aging Index (AAI; [1]). The AAI assesses how well the potential of older people is realized in different member states in line with the prevailing policy agendas, focusing on adding active and healthy years to life. The World Health Organization (WHO) defined the goal of active aging policy in 2002 as follows: “Active aging is the process of optimizing opportunities for health, participation and security in order to enhance quality of life as people age”. The same document also states that “these policies and programs should be based on the rights, needs, preferences and capacities of older people” [2]. This definition emphasizes health, but it also places considerable value on opportunities to participate in meaningful activities according to the individual’s life situation.

In addition to the macro and meso levels discussed above (country, organizational and institutional levels), active aging can also be promoted at the micro level, i.e., in the everyday lives of individual people and families. Many people wish to remain active through engagement in a variety of activities [3], regardless of being in less-than-perfect health. We recently published a definition of active aging that echoes the spirit of the WHO’s macro-level definition but is focused on the individual (micro level): “active aging refers to the striving for elements of well-being through activities relating to a person’s goals, functional capacities and opportunities” [4].

People inherently strive for well-being by pursuing universal needs for competence, autonomy and relatedness [5]. However, the risk for decreased well-being due to passiveness and alienation increases with increasing age, declining functional abilities, (real and perceived) barriers to participation and loss of social ties. Many older people report that preventing passiveness and encouraging participation may add years to life and enhance well-being [6, 7]. Participation in life situations is one of the key dimensions of quality of life in old age [1, 2] and increasing evidence suggests that any meaningful activity is beneficial for different aspects of well-being in older people [8, 9].

We chose individualized counselling as a method for promoting active aging at the micro level, as it provides a feasible and cost-effective way to advance autonomous motivation for self-chosen activities. In the present study, the aim of counselling is to help the participant to increase awareness of meaningful and desirable activities that are likely to yield personal well-being, and to set new self-selected activity goals, foster autonomous motivation and facilitate positive changes in activity.

Earlier counselling studies aiming at increasing activities and participation among older people have mostly concerned participation in physical activity and other health behaviors or have targeted people with specific chronic conditions [10, 11]. Successful interventions have typically incorporated tailored counselling based on theory and personal contact [10–13]. A recent meta-analysis found that health promotion interventions delivered face-to-face and including behavior change techniques such as goal setting, self-monitoring or behavioral practice/rehearsal, or combinations of these, were associated with beneficial changes in multiple motivational constructs [14]*.*

Motivation is a psychological concept defined as ‘a driving force for the goal-directed behavior’ [15]. Influencing motivation in counselling interventions is essential, as it underlies the efforts to change behaviors [14]. Autonomous motivation is linked with positive changes, e.g. in physical activity, and refers to engagement based on pleasure or personal importance to the individual rather than extrinsic control, such as fear of punishment [5]. The integration of two socio-cognitive theoretical models, the self-determination theory [5] and the theory of planned behavior [16], is used as the theoretical framework of the AGNES intervention. The Self-Determination Theory (SDT) is a motivation theory and is concerned with supporting our natural or intrinsic tendencies to behave in effective and healthy ways, whereas the Theory of Planned Behavior (TPB) links one’s beliefs and behavior. A previous meta-analysis provided evidence supporting the integration of the two theories [17], and hence their integration is expected to provide complementary explanations of the processes that underlie motivated behavior. Although the SDT framework has been widely used to explore and explain the motivation behind everyday activities in older people [18–20] and the TPB to explain how older individuals intend to behave [21–25], the integrated model has hitherto only been used as a process model in seeking to explain the behavior of older adults [26]. There is a lack of intervention research testing the integrated model’s ability to explain behavior change in older adults across time.

Our view is that increased activity will also increase well-being. While the dictionary definition of well-being is “a good or satisfactory condition of existence”, in empirical research, well-being is often assessed as the absence of specific indicators of ill-being such as depressive symptoms [27]. Increasing participation in various valued social and leisure activities may alleviate depressive symptoms [28]. Positive indicators of well-being include psychological well-being, which is characterized by, for example, a striving to find one’s true nature, personal growth and autonomy, and purpose in life [29]. However, there is less evidence on how to promote positive aspects of well-being. As our goal is to promote activities in line with a person’s goals and values and to support autonomy, it is likely that achieving this goal will also improve psychological well-being.

The World Health Organization defines quality of life as “the individual’s perception of their position in life in the context of the culture and value systems in which they live and in relation to their goals” [30]. Quality of life is a generic and multidimensional concept, and is often assessed as an outcome in different health enhancing interventions [31]. Due to the breadth of the concept, many different interventions targeting a wide range of activities have been found to improve quality of life among older people [3, 31–33].

Mobility refers to movement in all its forms, such as walking for leisure, daily tasks, activities associated with work and play, exercising, driving a car, and using various forms of public transport. Optimal mobility means the ability to go safely and reliably where one wants to go, when one wants to go, and how one wants to get there [34]. Life-space mobility, the spatial aspect of mobility, is an indicator of access to community amenities and describes a person’s opportunities to participate in meaningful activities outside the home [35, 36]. Consequently, increased participation in meaningful activities will likely increase life-space mobility and physical activity, since moving out-of-home and further away has been associated with higher levels of physical activity among older people [9], regardless of the reason for going out or even the means of transportation.

### Aims

The aim of this study is to develop an individualized counselling intervention that supports older individuals to increase their participation in self-selected valued activities and their involvement in meaningful life-situations and to test its feasibility and effectiveness. Specifically, we will investigate the effects of the intervention on active aging (primary outcome) as well as on well-being, depressive symptoms, quality of life, personal goals, mobility and physical activity (secondary outcomes). Moreover, we will examine the mechanisms underlying participants’ perceived autonomy support and active aging.

## Methods

### Setting

The study is community-based and targets older people whose life-space mobility is intermediate (excluding the most active and most inactive), have no cognitive impairment, and live independently in the municipality of Jyväskylä, Finland. These criteria have been selected as the intervention is expected to best benefit people who have room for improvement in their activity levels and whose physical and mental health allow them to comply with the intervention.

### Trial design

The AGNES intervention is a single-blinded, randomized, controlled, parallel-group, two-arm trial with a 1:1 allocation ratio. The parallel groups are a “Counselling group” (CG), serving as the intervention group, and a “Health information group” (HIG), serving as the control group.

### Blinding

Trained research assistants collecting data at all time- points will be unaware of the group allocation. The statistician performing the analyses will also be blinded to group allocation. After randomization, the participants and the counsellor delivering the intervention will be informed of the group allocation.

### Sequence generation and the allocation concealment mechanism

Stratified randomization for age and sex will be used with a 1:1 allocation to ensure a good balance of participant characteristics in each group. The randomization sequence will be created using Stata 15.0 statistical software (StataCorp, College Station, TX) by the study statistician, who immediately after generation of the random allocation sequence will seal them in envelopes.

### Sample size and power calculations

A total of 168 participants are needed for a 90% probability to detect a treatment difference at a two-sided 0.05 significance level, if the true difference in the main outcome between the intervention and the control group is 10%. As some of the participants may be vulnerable and the intervention is long, 200 participants will be needed to allow for the potential attrition rate of 20% during this time. The power calculations are based on estimates from two earlier studies [37, 38].

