### Participants

#### Eligibility criteria

The AGNES intervention will recruit participants from the ongoing AGNES cohort study [39], which is an observational study of three age cohorts (75, 80, and 85 years) living independently in the municipality of Jyväskylä, Finland. Inclusion criteria for the RCT study will be age 75 or 80, a baseline score between 52.3 and 90.0 on the University of Alabama at Birmingham Life-Space Assessment (LSA; [35, 40]), and a score of 25 or higher on the cognitive function test (MMSE; [41]). Recruitment has started in October 2017 and will continue until the number of participants reaches 200.

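### Randomising 200 allows for 16% attrition, not the stated 20%: at 20% loss 160 remain against the 168 required, a minor shortfall in power

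*Protocol article*

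**What the plan says.** Under Sample size and power calculations, the protocol article states: "A total of 168 participants are needed for a 90% probability to detect a treatment difference", "at a two-sided 0.05 significance level". To cover losses over the year it adds that "200 participants will be needed to allow for the potential attrition rate of 20% during this time".

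The figure of 200 is the working target. Eligibility criteria says: "Recruitment has started in October 2017 and will continue until the number of participants reaches 200". The Abstract also gives two hundred as the number recruited and randomised. Trial design describes a "two-arm trial with a 1:1 allocation ratio", so 168 means 84 per arm and 200 means 100 per arm.

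No section gives a larger target or a lower attrition rate.

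Two other sections bear on how much a loss matters. Data analysis plans intention-to-treat analyses with linear mixed models, full information maximum likelihood under a missing-at-random assumption, and multiple imputation if needed. The adherence plan says that people who want to discontinue will be asked whether they will stay for the assessments only.

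**The concern.** An allowance for attrition should leave the required number in the analysis once the assumed share has been lost. Here the required number (168), the assumed loss (20%) and the inflated target (200) are all stated together, and they cannot all hold.

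The power statement and the point at which recruitment stops both rest on this figure. If attrition reaches the level that the plan itself names, the number remaining falls below the number said to give 90% power.

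**Working it through.** **Inputs**, all from the protocol article:

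- Required number: 168 in total, 84 per arm (Sample size and power calculations; Trial design for 1:1).
- Power 90%, two-sided significance level 0.05 (Sample size and power calculations).
- Assumed attrition: 20% (same section).
- Number to randomise: 200 (same section, Eligibility criteria, Abstract).

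**Step 1. Reproduce the 200.**

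- Correct inflation: N / (1 - attrition) = 168 / 0.80 = 210. This does not give 200.
- Common slip: N x (1 + attrition) = 168 x 1.2 = 201.6. Rounded, this is close to 200 and is the likely origin, though the article does not show its formula.

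**Step 2. What 200 delivers.**

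- Remaining after a 20% loss: 200 x 0.80 = 160, or 80 per arm.
- Shortfall: 168 - 160 = 8 completers, or 210 - 200 = 10 randomised.
- Attrition that 200 covers: 1 - 168/200 = 16%.

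**Step 3. Power at 160.** The article does not print a standard deviation, but none is needed. Take the 168 at 90% as given, assume a comparison of two means, and rescale.

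- Signal-to-noise ratio at 168: 1.960 + 1.282 = 3.242.
- At 160: 3.242 x sqrt(160/168) = 3.242 x 0.976 = 3.163.
- Power: Phi(3.163 - 1.960) = Phi(1.203) = 88.6%.
- The same calculation with a noncentral t, again calibrated to 90% at 168, gives 88.5%.

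| Analysed | Per arm | Attrition from 200 | Power |
|---|---|---|---|
| 200 | 100 | 0% | 94.3% |
| 168 | 84 | 16% | 90.0% |
| 160 | 80 | 20% | 88.5% |

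**Step 4. Detectable difference.** At 90% power it grows by sqrt(168/160) = 1.025, that is by about 2.5%.

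**The case against.** The strongest reply is that the 88.5% describes a completers-only analysis, which the article does not plan. The active aging scale is measured before the trial, at 6 months and at 12 months. Under the planned mixed models and maximum likelihood, someone lost after the 6-month visit still contributes, and some who stop the intervention may stay for assessments. The true loss of power may therefore be below 1.5 points. This stands as a limit on the size of the problem. It does not repair the statement, because the sample size section inflates for attrition in the ordinary way and takes no credit for partial data. People lost before any follow-up visit would add little in any case.

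A second reply is that the 20% is only a potential rate. That is also fair: at 16% or less, 200 is enough, and with no loss power is about 94%. But the sentence claims cover for 20%, and at 20% it fails.

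A reader might go further and infer that the trial is underpowered, or that the 168 is itself unsound because the 10% difference comes without scale points or a standard deviation and the calculation is credited to two earlier studies. The documents support neither inference. A drop to about 88.5% does not make the trial underpowered. A condensed article commonly leaves the inputs behind a sample size to the full protocol, and the cited studies are not at hand, so nothing shows that their estimates were unsuitable.

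**Conclusion.** Wrong as written, minor severity. The inconsistency is certain, because it follows from three figures in one section and needs no outside input: 200 covers 16% attrition, and at 20% the trial has 160 completers, 8 short of 168.

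The effect on power is small, about 88.5% against 90%. That figure rests on three assumptions: the 168 is correct for 90% power, the primary outcome is compared as a continuous score, and only completers contribute. If the third is relaxed in line with the planned analysis, the loss may be smaller. The finding concerns the accuracy of the attrition allowance and does not call the design into question.

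**What to change.** Keep 200 and reword the sentence in Sample size and power calculations, for example:

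> With 200 participants randomised, about 16% attrition can occur before fewer than 168 remain. At 20% attrition 160 remain, and power on a completers-only basis is about 88.5%.

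This costs one sentence and a slightly less favourable figure. The Abstract and Eligibility criteria can stay as they are.

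If the sponsor wants to rely on the mixed-model or maximum likelihood analysis to make up the difference, that section should say so. Randomising 210 would also reconcile the figures, at the cost of ten more participants, but a gap of this size does not require it.

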### Participants

#### Eligibility criteria

The AGNES intervention will recruit participants from the ongoing AGNES cohort study [39], which is an observational study of three age cohorts (75, 80, and 85 years) living independently in the municipality of Jyväskylä, Finland. Inclusion criteria for the RCT study will be age 75 or 80, a baseline score between 52.3 and 90.0 on the University of Alabama at Birmingham Life-Space Assessment (LSA; [35, 40]), and a score of 25 or higher on the cognitive function test (MMSE; [41]). Recruitment has started in October 2017 and will continue until the number of participants reaches 200.

#### Recruitment process and informed consent

Participants in the AGNES cohort study [39] who have consented to future study requests will be assessed for eligibility for the RCT. Following the cohort study baseline assessments, eligible participants will be offered an opportunity to join the trial. Willing participants will receive a short verbal briefing and written information, including a consent form that they can read at their leisure. Within 2 weeks, the intervention counsellor will call potential participants to confirm their willingness to participate in the study and, if necessary, to provide them with additional information on the study. Once the participant will provided verbal consent, the pre-trial interview will be conducted over the phone. After the interview, the counsellor will open the randomization envelope and inform the participant about the treatment group. The signed written informed consent form will be returned by post or in person.

#### Data collection

Data collection will be performed at three time points: pre-trial, mid-trial (at sixth months), and post-trial (at 12 months) by trained research assistants. The pre-trial data will derive from a face-to-face interview in the participants’ homes, a postal questionnaire completed by the participant, 1 week of physical activity surveillance using accelerometers and the phone interview conducted by the counsellor. The mid-trial and post-trial data collections will be conducted using face-to-face interviews in the participants’ homes followed by 1 week of physical activity surveillance with accelerometers (post-trial only). The interviewers have participated in a training course on interviewing techniques suitable for use with older people, study ethics and safety as well as practice sessions. Incoming data will be monitored periodically. Figure 1 shows the data collection timeline in months and participant contacts by group.

**Fig. 1 Fig1:**

Approximate timeline of data collection in months and participant contacts by group in the AGNES intervention. Participant contacts are indicated with vertical lines

### Intervention

The active aging counselling intervention targets several different behaviors that vary between individuals. Consequently, we follow the guidelines of the Medical Research Council (MRC) framework for complex interventions [42] and implementation research [43–45]. A central key aim of the AGNES intervention is to support older individuals’ autonomous motivation in seeking to participate in activities that they personally value. Individuals have a key role in setting their goals, planning their actions and monitoring their progress in change process. Another key issue is the individualization of the counselling sessions (face-to-face and phone calls) after profiling the participants, in order to better meet their needs. Profiling is defined as “the recording and analysis of a person’s psychological and behavioral characteristics, so as to assess or predict their capabilities in a certain sphere or to assist in identifying categories of people” [46]. The profiling sources are participants’ baseline data on the main areas of their everyday life such as health, social contacts, well-being, and preferred activities and goals.

#### Counselling group (CG)

After randomization, the intervention (CG) group will participate in a 90-min, face-to-face, individual counselling session on the premises of the University of Jyväskylä. A trained counsellor with previous experience in counselling older adults will deliver all the counselling sessions. The counselling session follows a semi-structured protocol of questions. The main body of the questions initiating discussion topics is the same for all participants. Additional probing questions will be based on the participants’ answers. The main body of questions guiding the counselling session consists of four sections, (a) Introduction and building rapport; b) Current activities and change talk; c) Goal setting, action plans and how to use the supportive materials that we provide (booklet, calendar and newsletter); and d) Wrapping up and closure. During the face-to-face counselling sessions, participants will receive an *information booklet* on active aging [47] from the counsellor. The Information Booklet is 64 pages long and provides information about activities and behaviors that promote active aging, with self-help exercises and techniques that the participants can use to facilitate their planned changes, and a calendar that they can use to monitor their activities. Participants will be instructed to use the information booklet as support during the one-year intervention.

After the initial face-to-face session, participants will receive four phone counselling sessions, at 1, 3, 6 and 9 months after the face-to-face counselling session. The aim of the sessions is to provide them with additional support, feedback and encouragement. The content of the follow-up phone calls will be a discussion about the participant’s progress towards achieving their goals, sharing in their successes or failures, and further encouragement to continue their efforts towards increasing their activities. The duration of these short counselling contacts is expected to be 20–30 min. In addition, participants will receive four printed newsletters, the first during the first counselling session, and the other three by mail 1 week before the phone sessions at 3, 6, and 9 months. The newsletters will feature the activities that are currently organized for older people in the Jyväskylä area and the success stories of people who are living an active life. A description of the Behavior Change Techniques (BCTs) used in the AGNES intervention [48] is displayed in Table 1.

**Table 1 Tab1:** Behavior change techniques (BCTs^a^) in the AGNES intervention

Group	Behavior change techniques	Face-to-face counselling	Information booklet	Phone counselling	Newsletter
Goals and planning	Goal setting (behavior)	X	X		
	Problem solving	X	X	X	
	Action planning	X	X	X	
	Review behavior goals			X	
	Discrepancy between current behavior and goal			X	
Feedback and monitoring	Self-monitoring of behavior	X	X	X	
Social support	Social support (unspecified)	X		X	
	Social support (practical)	X	X	X	X
	Social support (emotional)	X	X	X	
Natural consequences	Monitoring of emotional consequences	X	X	X	
	Information about health consequences		X		
	Information about social and environmental consequences		X		
	Information about emotional consequences		X		
Identity	Incompatible beliefs	X			
	Valued self-identity	X	X		
Associations	Prompts/cues		X		
Repetition and substitution	Habit formation		X		
	Generalization of a target behavior		X	X	
	Graded tasks		X		
Comparison of outcomes	Credible source		X		X
	Pros and cons		X		
	Comparative imagining of future outcomes		X		
Reward	Self-reward		X	X	
	Social reward			X	
Antecedents	Restructuring the physical environment		X		
	Restructuring the social environment		X		
Comparison of behavior	Social comparison				X

^a^BCTs Version 1

